#### Hypotheses

We hypothesize that at 2 years, EHA provides a superior OES compared with ORIF by at least a difference of 15.

#### Data analysis

No interim data analysis will be carried out before the analysis at 2 years. Baseline characteristics and outcome scores will, for each group, be summarized by number and percentage (categorical data) and mean and standard deviation or median and interquartile range, as appropriate (continues data). No statistical tests of differences in baseline characteristics between the two groups will be conducted as any difference must be due to chance and not bias. The differences in outcome scores between the two groups will be analyzed with use of parametric statistics (Students *t*-test) or non-parametric statistics (Mann-Withney U-test) as appropriate. Categorical data will be analyzed with use of chi-square test.

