### Randomization and concealment of allocation

Based on the sample calculation, we intend to include a total number of 44 patients allocated into two groups of equal size:
EHA (elbow hemiarthroplasty)—intervention groupORIF (open reduction and internal fixation)—comparator group

The randomization is done just prior to the operation by the primary investigator, who will inform the operation team about the intended surgery. The randomization sequence will be computer generated using RED-Cap (Research Electronic Data Capture) program. The patients will be randomized using stratified, block randomization with a 1:1 allocation ratio and stratified according to age in years (50–69, 70 and above) and sex. The randomization sequence is generated by a statistician, and the patients will be stratified and then randomized. After randomization, the patient’s allocation will be revealed to the operation team to unpack the necessary operation tools and prosthesis.

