### Outcome measures

#### Primary functional outcome

The Oxford Elbow Score (OES) will be used to assess the primary outcome at 2 years.

The OES is a 12-item, patient-administrated questionnaire that measures the quality of life in patients with an elbow disorder. There are three unidimensional domains: elbow function, pain, and social-psychological status [5, 13]. Each question is answered on a five-point scale with each question contributing equally to the total score. Thus, the total score ranges from 12 to 60, with 60 being the worst. For ease of presentation the score is converted to a scale from 0 to 48 with 48 being the best. The outcome can be interpreted based on a 48-point scale: 0–19, poor; 20–29, fair; 30–39, good; and 40–48, excellent [6]. The Danish version, which will be used in this study, has been translated and culturally adapted according to the guidelines by Guillemin, Bombardier, and Beaton [6, 21].

The minimal clinically important differences (MCID) for the total score of OES has not been defined, but Dawson et al. reported the MCID for each of the three domains, pain, function, and social-psychological. The MCID for the three domains was 19, 9, and 18, respectively [5]. Accordingly, we estimated the MCID for the total score to be 15.

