### Statistics

#### Sample size calculation OES

Oxford elbow score (OES) will be used to measure the primary outcome.

Sample size calculation was performed with a standard deviation (SD) of 16, a MCID of 15, a significance level at 0.005, and power of 0.80, resulting in 18 participants in each group (44 participants in all with allowance for 18% drop-out).

The estimation of SD = 16 is extrapolated from a study on 24 patients with distal humeral fractures treated with EHA [1]. There is no MCID defined for the total score of OES, but Dawson et al. have reported the MCID for each of the three domains—pain, function, and social-psychological—for a group of patients with different pathologies including TEA for osteoarthritis and rheumatoid arthritis. MCID for the three domains is 19, 9, and 18, respectively [5]. Accordingly, we chose the MCID to be 15.

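### Randomisation is stratified by age group and sex, but the stated between-group tests ignore both; the tests stay valid but lose power if these factors predict the Oxford Elbow Score

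*Protocol article*

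**What the plan says.** - Protocol article, Randomization and concealment of allocation: patients are allocated by "stratified, block randomization with a 1:1 allocation ratio and stratified according to age in years (50–69, 70 and above) and sex". Two age bands and two sexes make four strata. No block size is given.
- Primary functional outcome: "The Oxford Elbow Score (OES) will be used to assess the primary outcome at 2 years".
- Data analysis: "The differences in outcome scores between the two groups will be analyzed with use of parametric statistics" or a rank-based alternative; in full, the tests named are "parametric statistics (Students *t*-test) or non-parametric statistics (Mann-Withney U-test) as appropriate". For the rest, "Categorical data will be analyzed with use of chi-square test".
- Sample size calculation OES: the inputs include "a standard deviation (SD) of 16, a MCID of 15". The result is 18 per group, or 44 in all with 18% drop-out.
- Hypotheses: "EHA provides a superior OES compared with ORIF by at least a difference of 15".

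No section adjusts for age group or sex, or stratifies any analysis by them.

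**The concern.** Blocking within age-by-sex strata keeps the arms nearly balanced on those factors. Differences between strata therefore contribute little to the true sampling error of the treatment difference. The ordinary t-test does not know this: its standard error comes from the whole within-arm spread, which still contains the between-stratum variation. If age group or sex predicts the OES, the standard error is too large, the test rejects too rarely under the null, and the interval is wider than it needs to be.

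The stake is efficiency, not validity. The trial is small, and its Discussion names avoiding a type II error as an aim. Power that could be recovered without recruiting another patient is worth having.

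**Working it through.** **Inputs from the protocol:** SD 16; difference 15; power 0.80; 18 per group; 44 randomised; 18% drop-out; 1:1 allocation; four strata.

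**Assumptions, because the protocol does not give them:** blocks of 4; stratum shares of 15/35/10/40%; loss at random; normally distributed scores; and a share of OES variance explained by age group and sex (R²) from 0 to 0.3. Two-sided alpha is taken as 0.05, for the reason in step 1.

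**1. The plan's own figure.** n per group = 2(z₁₋α/₂ + z₀.₈₀)²(SD/difference)².
- Alpha 0.05: 2(1.960 + 0.842)²(16/15)² = 17.9, so 18 per group; 36/0.82 = 43.9, so 44. This reproduces the plan.
- Alpha 0.005, as printed: 2(2.807 + 0.842)²(16/15)² = 30.3, so 31 per group. This does not reproduce the plan.

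The printed alpha is a separate issue. The calculations below use 0.05 because the stated sample size matches it.

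**2. What the formulas predict at 18 per group.**
- Unadjusted SE = 16√(2/18) = 5.33. The 95% interval width is 2 × 2.032 × 5.33 = 21.7 points, whatever R² is.
- Adjusted SE ≈ 5.33√(1 − R²). At R² = 0.2 this is 4.77, and the width is 2 × 2.037 × 4.77 = 19.4 points.
- With perfect balance, the unadjusted test's effective critical value is 1.96/√(1 − R²). At R² = 0.2 this is 2.19, a type I error of about 2.8%. Incomplete blocks and losses weaken the balance, so the true figure lies somewhat closer to 5%.

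**3. Simulation.** Forty-four patients were randomised in stratified blocks and 36 analysed, with 12,000 trials per setting under the null and 6,000 at a 15-point difference. The unadjusted t-test was compared with a linear model containing treatment, age group and sex.

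| R² | Type I error, unadjusted / adjusted | Coverage, unadjusted / adjusted | Mean interval width (points), unadjusted / adjusted | Power, unadjusted / adjusted |
|---|---|---|---|---|
| 0 | 5.0% / 4.9% | 95.0% / 95.1% | 21.6 / 21.8 | 77% / 76% |
| 0.1 | 4.3% / 5.3% | 95.7% / 94.7% | 21.6 / 20.7 | 78% / 81% |
| 0.2 | 3.4% / 5.0% | 96.6% / 95.0% | 21.6 / 19.5 | 80% / 86% |
| 0.3 | 2.5% / 5.0% | 97.5% / 95.0% | 21.7 / 18.2 | 80% / 89% |

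Repeat runs agreed to within about a point on power. At R² = 0 one gave 78% for both analyses. A run with four equal strata gave an unadjusted type I error of 3.1% at R² = 0.3.

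**4. If all 44 are analysed.** The pattern is the same from a higher base: power is 86% / 85% at R² = 0, 86% / 89% at 0.1, 88% / 92% at 0.2 and 89% / 95% at 0.3.

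**5. The permitted rank test.** A further simulation at R² = 0.2 (5,000 trials, same shares and blocks, normal scores) gave type I errors of 2.9% (t-test), 2.5% (Mann-Whitney) and 4.7% (adjusted model), with power of 80%, 76% and 86%. The rank test is no less conservative.

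**The case against.** The strongest reply is that nothing here is invalid. In no setting did the unadjusted test exceed its nominal level or under-cover by more than simulation noise, and if the strata are not prognostic it is correctly calibrated. A reader might infer that the trial's error rate and intervals are simply wrong. The protocol does not support that: any error is in the conservative direction, and it appears only if age group or sex predicts the OES. This part of the reply stands.

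A reader might also infer that the stratification is wasted. It is not. It still balances the arms and lowers the true variance of the difference. Unadjusted power at 36 patients rose from 77% to 80% as R² went from 0 to 0.3, so the trial does not fall below its planned power by ignoring the strata. What it forgoes is an additional gain.

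It would likewise be wrong to call 78% the best power available. That is the t-based figure at 18 per group, the lower end; at 22 per group it is 86%. The protocol carries the last observation forward for drop-outs after 3 months, so the number analysed may be nearer 44 than 36.

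The size of the gain rests on an assumed R². That stands too, and it is why a range is shown.

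Finally, the choice between t-test and Mann-Whitney has no stated criterion. A selection rule is the sort of detail a statistical analysis plan usually supplies, and the protocol says the data analysis will be blinded, so that is not pressed here. On a bounded 0–48 score in a small trial, keeping a rank test available is defensible. The omission of the strata is different: the protocol names specific tests, and neither uses them.

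**Conclusion.** The mismatch between stratified design and unstratified analysis is in the text. The consequence is a valid, unbiased comparison that may be inefficient. At 36 analysed, adjustment gains about 3 points of power if the strata explain 10% of OES variance, about 6 at 20% and about 9 to 10 at 30%, and nothing if they explain none. These figures depend on the assumed alpha of 0.05, normal scores, random loss, block size and stratum shares. The direction follows from the design; the amount cannot be read from the protocol. This is a near-costless improvement that should be made. It is not a flaw that threatens the trial's conclusions.

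**What to change.** In Data analysis, state that the primary analysis of the 2-year OES is a linear model with treatment, age group (50–69, 70 and above) and sex, reporting the adjusted mean difference (EHA minus ORIF) with its 95% confidence interval. Use the same covariates for the continuous secondary outcomes: Mayo Elbow Performance Score, pain on the visual analogue scale, and range of motion. A rank-based test may be kept as a sensitivity analysis.

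The cost is a sentence or two of wording and two degrees of freedom. If the strata turn out not to be prognostic, at most about one point of power is lost. Age and sex are already recorded before surgery and used for the randomisation, so no new data are needed and the sample size does not change.

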## Discussion

We will attempt to avoid the type-II error (when the hypothesis testing does not reject the null hypothesis, even though the null should have been rejected) by using a proper sample size and by adding 18% to sample size compensating for drop-outs. The drop-out bias will be minimized by obtaining permission to call patients who do not show up for subsequent follow-up and also to visit the patients at home. Selection bias will be avoided through randomization. If ORIF during the surgery is regarded to be technically impossible, the procedure can be converted to EHA. In order to follow the principle of the intention-to-treat, the patient will continue to be in the ORIF group and included in the analysis according to the randomization. A secondary analysis will be conducted on a per protocol basis where only patients who undergo surgery according to the randomization are included.

The consequences of having unblinded patients are unknown. It may introduce bias to the study, which, in most cases, will be in favor of the intervention. In the present study, the intervention and the comparator are surgery and the patients and blinding of the patients may not be as important as in studies where surgery is compared with non-surgery. The primary outcome is a patient-administered questionnaire and does not involve any persons affiliated with the study. It was chosen as the primary outcome to avoid observer bias. The secondary outcomes are not observer blinded and the results will be interpreted carefully due to the risk of bias.

The trial will provide high-quality evidence regarding the short- and long-term clinical and patient-reported outcomes of ORIF and EHA. We use the same outcome scores as in previous randomized trials comparing TEA and ORIF [8, 9, 17]. This makes it possible not only to compare the results but also to include the results in future systematic reviews and meta-analyses. We believe that the results from the present trial, together with results from other randomized trials, can be used to establish a treatment algorithm for distal, intraarticular humerus fractures.

### Trial status

Protocol version 4.

Issue date: 28/04/2020, author [name].

Inclusion started on February 1, 2020. Finnish date of recruitment of all patients is expected to be at December 31, 2022. In case the target number of 44 patients has not been met, the recruitment period may be extended to reach the number required. The trial processes will be monitored by the primary investigator and the study group to ensure the protocol. If any changes are necessary, the primary investigator is obliged to inform The Scientific Ethical Committee of the Capital Region of Denmark and Data Protection Agency.

## Data Availability

All study-related information will be stored securely on the study site, including all completed paper forms. Study data will be collected and managed using REDCap electronic data capture tools and EPIC hospital clinical digital journal system hosted in the Capital Region of Denmark. REDCap is a secure, web-based application designed to support data capture for research studies. Identifying information of the patients will be stored in the hospital’s secured intranet system. Study information will not be released without the permission of the relevant participant. The primary investigator will do the data collection and will have access to the trial materials and final dataset. The study is approved by the Danish Data Protection Agency, and it will follow General Data Protection Regulation and Data Protection Act. After the completion of the study, the results will be made available for meta-analysis and systematic reviews.

## Abbreviations

EHA: Elbow hemiarthroplasty
ORIF: Open reduction and internal fixation
TEA: Total elbow arthroplasty
OES: Oxford Elbow Score
MEPS: Mayo Elbow Performance Score
VAS: Pain severity score
CT: Computerized tomography
RED-Cap: Research Electronic Data Capture
MCID: Minimal clinically important differences
ASA: American Society of Anesthesiologists Score
AO/OTA: Arbeitsgemeinschaft für Osteosynthesefragen/Orthopaedic Trauma Association
